## **9.4 Discontinuation of trial treatment and patient withdrawal**

Discontinuation of trial treatment or withdrawal of consent by patients for any reason should be communicated to the PIONEER office as soon as possible by telephone, fax or email.

[figure not shown]

#### 9.4.1 Discontinuation

Patients should discontinue trial treatment in the following circumstances and this should be reported in the End of Trial Medications Case Report Form (CRF):

1. If the Investigator decides that the patient should be discontinued from the treatment at any point due to an inter-current illness or if continued participation in the trial will result in delay to planned tumour excision.
2. Any CTCAE Grade  $\geq 3$  drug related toxicity which does not resolve to Grade 1 or less within 72 hours (except where supportive measures exist to control the toxicity which had not been adequately instigated at the time of the AE, e.g. antiemetics for nausea and vomiting or anti-motility agents for diarrhoea).
3. If the patient withdraws from the trial, refuses baseline core biopsy (only applies when diagnostic tissue is not available), opts to discontinue the treatment or chooses not to comply with trial procedures.
4. If the patient's disease is progressing while on trial treatment.

Patients who have been discontinued from the trial treatment and are experiencing ongoing toxicity from Letrozole and/or Megestrol acetate will be followed up as clinically indicated until the toxicity resolves to Grade 1, or less. Patients who have completed the minimum 13 days of treatment (or  $\geq 80\%$  days of dosing if 16 to 19 days of treatment) prior to developing toxicity will continue to attend scheduled follow ups and procedures (unless decided otherwise by the clinician) and their samples/data will be used for analysis.

However, patients who do not complete at least 13 days of the full 15 day pre-operative window dosing schedule (or  $\geq 80\%$  days of dosing if 16 to 19 days of treatment) won't be considered evaluable for the primary endpoint. For patients whose treatment is extended beyond 15 days (up to 19 days), the minimum number of days in which the patient should dose with trial treatment must be greater than 80% of the full treatment window e.g. for 19 days of treatment a minimum of 15 days of study drug must be taken. These patients' samples and data will be retained and may be used for analysis of the secondary and exploratory endpoints. Patients whose treatment is scheduled for 13 days must complete the full treatment window to be evaluable for the primary endpoint (i.e. no treatment doses can be missed).

#### 9.4.2 Withdrawal of consent

Patients may withdraw their consent to participate in the trial at any time. If the patient explicitly states their wish to withdraw from receiving any further trial-specific treatment, the Investigator should inform the PIONEER office promptly and complete the Withdrawal Form. If the patient withdraws consent for participation in the trial, then no further trial procedures will be undertaken and no data or samples will be collected from the time of withdrawal.

However, data and samples collected up to the time of consent withdrawal will be included in the data reported for the trial.

### **10 Procedures and assessments**

Patient recruitment, consent and screening will occur within the oncology or surgical unit, depending on the participating site.

[figure not shown]

Patients will be identified as potentially eligible for participation at a breast cancer surgical MDT meeting, and approached for discussion after being informed of the results of their diagnostic core biopsy confirming ER-positive breast cancer. This initial discussion may occur with the Principal Investigator (PI) or a qualified member of the research team.

If patients are agreeable to participation in the trial they will be provided with a Participant Information Sheet (PIS) and another appointment will be booked by the trial team to discuss participation further and to undertake written Informed Consent (IC) if required.

Once written IC for all study procedures and treatments has been obtained, the participants will undergo screening assessments, including blood tests.

Eligible patients will be randomised to a trial treatment (eligibility confirmation required from central coordinating office). A research tissue from the diagnostic tissue block (up to 2 months before patient starting treatment) will be required. If patient does not have available tissue from diagnosis, they will undergo a baseline research biopsy. Baseline research biopsy may occur before or after randomisation but must be after central coordinating office confirmation.

Trial treatment will then begin on Day 1, patient treatment compliance and an assessment of AE's will be checked by telephone on Day 5 (+/- 1) and Day 10 (+/- 1), and then the patient will undergo tumour excision and/or a core biopsy on Day 15 (+ ≤4 days). Patients will return for a post-treatment follow-up visit/ phone call on Day 28 (+/- 5 days), two weeks after tumour excision and/or core biopsy. Treatment can be planned for 13-14 days in the exceptional circumstance that tumour excision or Day 15 biopsy can not be scheduled on Day 15 (+ ≤4 days).

Patients in Cohort A will follow standard post-operative procedures as per local policy and SOPs. If standard local practice includes a two week post-operative visit, this two week visit will be arranged on the same day (where possible).

SAEs should be reported from the point of IC, so safety/AE/SAE review should be included during every visit.

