## **9.3 Treatment Assignment and Randomisation Number**

Eligible patients will be randomly assigned, using a minimization method with a random element, to either the control arm (Letrozole alone) or one of the two research arms (Letrozole with Megestrol Acetate at low and high dose) in a 1:1.5:1.5 ratio.

The stratification factors are:

- tumour grade (1,2,3),
- ductal vs. lobular subtype,
- intensity of ER staining (3-6, 7-8), reported on the initial diagnostic core biopsy, to ensure that each arm of the trial is well balanced.

Randomisation must be complete prior to the start of trial treatment.

Randomisation will be implemented using a web-based central randomisation system by the relevant participating site staff. The web-based central randomisation system will allocate patient treatment arm and trial numbers sequentially in the order in which the patients are randomised.

At the site initiation, the trial coordinator will train site staff in how to access and use the randomisation system.

This is an open-label trial. The histopathologist assessing the biological response (primary endpoint, Ki67 expression by IHC; secondary endpoint, Caspase-3 by IHC) will, however, be blinded as to treatment allocation.

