### 10.1.2 Subject Registration/Randomisation

Registration and randomisation must be complete prior to the start of trial treatment. Patients will be registered following confirmation of eligibility (including results of screening assessments). Local site staff will complete the 'patient details', 'informed consent' (CRF not original consent form) and 'eligibility' CRFs and forward them to the central coordinating office to register the patient and provide authorisation to randomise. Appropriate staff at the local site will then randomise the patient upon confirmation of central approval. Data will be entered into a web-based central randomisation system (Sealed Envelope) by the relevant local site staff. The web-based central randomisation system will allocate patient trial numbers sequentially in the order in which the patients are randomised.

Supporting documentation required for patient randomisation will include results of an initial diagnostic core biopsy, specifically delineating ER status, histological subtype (ductal or lobular) and tumour grade, in addition to the patient details, IC and eligibility forms. These must be medically reviewed to confirm randomisation. Any queries must be resolved prior to randomisation. The PI or co-investigator will sign the eligibility CRF to confirm eligibility.

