### 10.2 **Baseline assessments – Prior to Treatment (Day -15 to Day 1)**

Baseline assessments may be performed on the same day as screening provided patient eligibility has been confirmed. For patients in Cohort A, the date of tumour excision must be planned carefully to be performed 15 days (+  $\leq 4$  days) from the start of the trial treatment.

The following data points are to be recorded:

- a) Baseline symptoms (non treatment-related, disease-related)
- b) Weight in kg and height in cm
- c) Concomitant medications
- d) AEs/SAEs
- e) Baseline research core biopsy of breast tumour (before or after randomisation) if patient does not have available research tissue from the diagnosis (see section 16).
- f) Trial treatment may be dispensed (up to Day 1 of trial involvement)

Please refer to Section 16 for more information regarding the **Storage and Analysis of Samples**.

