## **13 Evaluation of Results (Definitions and response/evaluation of outcome measures)**

### **13.1 Trial Outcome Measures**

#### 13.1.1 Primary efficacy outcome measure

Change in tumour proliferation measured by Ki67 immuno-histochemical assessment (%) at baseline compared to Day 15 (+  $\leq 4$  days).

Ki67 expression will be measured centrally, blinded with treatment allocation, using formalin-fixed, paraffin embedded histopathology sections of the tumour tissue specimens taken at baseline and at Day 15 (+  $\leq 4$ ) days. Additional analyses will also be done on the tumour biopsy specimens taken at breast tumour excision (or the additional research biopsy if tumour excision is not performed on Day 15 +  $\leq 4$  days). IHC for the Ki67-proliferation associated antigen will be carried out on 3-4  $\mu\text{m}$  sections of the routinely processed material following heat mediated antigen retrieval and with the appropriate primary antibodies.

The tumour-cell Ki67 antigen labeling index will be recorded following the

[figure not shown]

recommendations from the International Ki67 working group [19]. Sections from the diagnostic or baseline core biopsy, Day 15 (+  $\leq 4$ ) tumour biopsy/post-surgical specimen will be stained for Ki67. Tumour cell nuclei showing any intensity of staining will be regarded as positive. The stained slide will be reviewed at low power and representative high power fields (x40) will be selected for counting; if there are clear areas with an increased proportion of cells staining (hot spots) these will be included in the count. One thousand tumour cell nuclei will be counted; if there are less than 1000 tumour cells in a biopsy a minimum of 500 will be counted. If there are less than 500 cell nuclei then further sections will be stained at a depth of 25 $\mu$ m and counted until the minimum number of cells is reached. Ki67 will be scored as the percentage of tumour nuclei staining. The investigators analyzing Ki67 will be blinded as to treatment allocation. Ki67-response is defined as a 50% or higher fall in Ki67 expression.

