## **16 Storage and Analysis of Samples**

The collection of pre and post treatment tumour tissue specimens are mandatory and part of the clinical trial. A research tissue from the diagnostic core biopsy (up to 2 months before patient starting treatment) will be required. Approximately 10 unstained slides are needed.

If archive diagnostic tissue blocks are provided, will be returned to the original pathology department at the end of the trial.

[figure not shown]

For patients who do not have tissue available from diagnosis, a research pre-treatment breast core biopsy will be obtained at baseline (Day -15 to Day 1). It is recommended that the tissue is obtained by ultrasound guided biopsy, when possible at the same time as surgical clip insertion (if required). For each biopsy, up to 5 passes (and a minimum of 2) will be acquired using a core biopsy needle as per institutional guidelines. At least 1 core should be fixed in 10% buffered neutral formalin.

Addenbrooke's patients only: The remaining cores should be snapped frozen in liquid nitrogen or on dry ice, transferred to a properly marked cryovial and stored in a -80°C freezer. Anonymised research samples will be stored in a -80°C freezer in a central facility in the Cambridge Institute (CRUK) Biorepository.

Similarly, post treatment samples will also be obtained, preferably during tumour excision to minimise the impact on the patient. More biopsy tissue may be acquired from the surgical specimen (up to 10 passes and a minimum of 2) depending on the size of the tumour.

It is recommended that tumour biopsies in formalin should remain in 10% neutral buffered formalin to ensure adequate fixation (as per local processes) and compatibility with pre-optimised downstream IHC methods, following which they can either be processed through to paraffin wax and embedded into a wax block immediately or first transferred to a 70% ethanol solution to be processed/embedded within a 72 hour window (as per local processes). Formalin fixed paraffin embedded tissue should be shipped ambient when available or samples can be grouped and sent in batches.

Research samples must be anonymised with a patient trial number, date of birth and initials before being sent by mail to the PIONEER Office.

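### For patients without diagnostic tissue, the baseline biopsy may follow open-label randomisation, so refusers can leave the primary analysis knowing their arm

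*Protocol*

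**What the plan says.** The primary endpoint is the change in Ki67 from baseline to Day 15, so each patient needs a pre-treatment sample. Protocol section 13.1.1 takes the baseline reading from either of two sources: "Sections from the diagnostic or baseline core biopsy". The diagnostic core is the default. Section 16 states: "A research tissue from the diagnostic core biopsy (up to 2 months before patient starting treatment) will be required". Section 10 gives the fallback: "If patient does not have available tissue from diagnosis, they will undergo a baseline research biopsy".

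On the timing of the fallback biopsy, section 10 says: "Baseline research biopsy may occur before or after randomisation but must be after central coordinating office confirmation". Section 10.2(e) lists: "Baseline research core biopsy of breast tumour (before or after randomisation) if patient does not have available research tissue from the diagnosis". Footnote 5 to the schedule in section 10.6 gives the same latitude.

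Three other provisions matter:

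- Section 9.3: "This is an open-label trial". Site staff randomise through a web system that returns the arm.
- Section 9.4.1, item 3, makes it a reason to discontinue trial treatment if the patient "refuses baseline core biopsy (only applies when diagnostic tissue is not available").
- Section 10.1.2 sets the documents needed to randomise: "Supporting documentation required for patient randomisation will include results of an initial diagnostic core biopsy". It asks for results. It does not ask whether usable tissue can be obtained.

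**The concern.** For a patient without diagnostic tissue, the research biopsy supplies the baseline half of her primary outcome. If it is scheduled after randomisation, she and the site know the arm when she decides whether to go through with an extra invasive procedure. A patient disappointed with letrozole alone, or uneasy about megestrol, can decline at that point. The protocol foresees refusal and answers it by stopping treatment.

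What is at stake is comparability. Minimisation balances the arms at allocation and cannot correct a loss that happens afterwards for reasons linked to the arm. Recruiting another patient restores the count but not the balance. A missing pre-treatment sample also cannot be recovered once treatment has begun.

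**Working it through.** **Tracing the rule**

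1. No diagnostic tissue is available, so a research biopsy is needed (sections 10, 10.2(e), 16).
2. That biopsy may come after randomisation (sections 10, 10.2(e), 10.6 footnote 5), and the arm is then known (section 9.3).
3. Refusal leads to discontinuation of trial treatment (section 9.4.1, item 3). The biopsy is pre-treatment, so the patient has taken no trial doses.
4. She cannot reach 13 days of dosing, so she is not evaluable (section 9.4.1) and is excluded and replaced (section 11.2).
5. The primary t-test uses evaluable patients only (section 14.1).

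Nothing in the protocol makes the later timing necessary. Both the biopsy and randomisation must follow central confirmation (sections 10, 10.1.2), and both precede Day 1.

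**The plan's own sample size**

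Inputs from section 14.2: difference 0.775 − 0.66 = 0.115, SD 0.242, one-sided α 0.025, power 80%, A:(B+C) = 1:3. The two-sample formula gives 47 in Arm A and 188 in total, against the stated 189. With 47 and 142 patients, noncentral-t power is 80.2%. Randomising 189/0.90 = 210 matches the plan.

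The standard error of the A versus B+C difference is 0.242 × √(1/47 + 1/142) = 0.0407, or 4.1 percentage points.

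**Illustrative bias**

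The protocol gives no share needing the biopsy and no refusal rates. These are assumptions:

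- share s needing it: 10%, 20% or 30%;
- refusal among them: 20% in Arm A, 5% in Arms B+C;
- mean Ki67 reduction of those lost differs from their arm's mean by one SD, d = 0.242, in the same direction in both groups.

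Loss in a group is f = s × refusal rate. Removing a fraction f whose mean lies d from the arm mean shifts the retained mean by f × d / (1 − f).

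| s | f, Arm A | f, B+C | Shift A | Shift B+C | Bias | Share of 0.115 |
|---|---|---|---|---|---|---|
| 10% | 0.020 | 0.005 | 0.0049 | 0.0012 | 0.0037 | 3% |
| 20% | 0.040 | 0.010 | 0.0101 | 0.0024 | 0.0076 | 7% |
| 30% | 0.060 | 0.015 | 0.0154 | 0.0037 | 0.0118 | 10% |

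For s = 20%: 0.04 × 0.242/0.96 = 0.0101; 0.01 × 0.242/0.99 = 0.0024; the difference is about 0.8 points, and 0.8/4.1 is about 0.2 of a standard error.

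Reversing the pattern (no refusal in Arm A, 20% in B+C) and taking bias as the difference in loss × 0.242, where those lost differ from those retained by one SD, gives 0.02 × 0.242 = 0.005 (4% of 0.115) at s = 10%. At s = 40% it gives 0.08 × 0.242 = 0.019 (17%).

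**Power**

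Suppose these losses came on top of the planned 10% and nobody was replaced. Arm A would have 52.5 × 0.9 × (1 − f) patients and B+C 157.5 × 0.9 × (1 − f). In the tabulated scenarios power is 79.7%, 79.0% and 78.3%, against 80.4% with no such loss. In the reversed pattern it is 80.1% at s = 10% and 79.5% at s = 40%. Section 14.4 continues recruitment to 189 evaluable, so even this small drop would largely be made up.

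**The case against.** The case against acting is substantial, and parts of it stand.

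- **Only a subset is affected.** A reader might infer that baseline Ki67 in general is collected after allocation. It is not: the diagnostic core is the default, and every randomised patient has had one. This stands and limits the point.
- **Consent comes first.** Agreement to donate tissue is an inclusion criterion (section 9.1), and consent to all procedures precedes screening (section 10). A refuser must go back on that. This lowers the likely number but does not close the route, because consent can be withdrawn (section 9.4.2) and section 9.4.1 provides for refusal.
- **Ki67 is read blinded.** True, but that protects scoring. It does not affect whether a sample exists.
- **Inadequate cores.** A reader might also infer that poor tissue yield would differ by arm. The documents do not support this. The sample is pre-treatment and read centrally and blinded, two to five passes are taken (section 16), and further sections are cut when nuclei are few (section 13.1.1). Any remaining shortfall should fall about equally across arms, and taking the core earlier would not cure it.
- **Other exits remain.** A patient unhappy with her arm can still stop treatment or decline the Day 15 biopsy. The change removes one route, not all.
- **Scheduling.** Surgery dates fix the treatment start in Cohort A, Cohort B should start as soon as feasible (section 5), and section 16 recommends combining the biopsy with clip insertion when possible. The flexibility has a plausible practical use, though the protocol does not say it is needed.

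**Conclusion.** The point holds as an avoidable risk confined to patients without diagnostic tissue. For them the protocol allows the sole source of baseline Ki67 to be refused after the arm is known, and its own rules then take the refuser out of the primary analysis.

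A reader might go further and conclude that dropout will be unequal or that the result will be biased. Nothing in the document shows that. The 0.4–1.2 points rest wholly on the assumed share, refusal rates and one-SD difference, and no passage links refusal to Ki67 response. With equal refusal in all arms and the same one-SD difference, the bias would be zero. The direction is also open. Even the 30% scenario stays below a third of a standard error (1.2/4.1 = 0.29), and power is barely touched. The reason to act is that the change costs very little, not that the expected harm is large.

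**What to change.** 1. In sections 10, 10.2(e) and 10.6 footnote 5, remove the option of taking the research biopsy after randomisation. Keep the existing requirement that it follow central confirmation of eligibility.
2. Add a condition to section 10.1.2: before the patient is randomised, either a diagnostic block or slides are confirmed available, or the research core has been taken. The order is then eligibility confirmation, baseline tissue secured, randomisation. Someone who declines the biopsy becomes a screen failure and not a randomised loss.

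The cost is an edit in three places and one item on the randomisation checklist. The same biopsy is done, only earlier, and the sample size of 189 evaluable from about 210 randomised is unchanged. Scheduling becomes slightly tighter for this subset, and a few patients may have the biopsy and then not be randomised.

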## **10.1 Screening evaluation**

### **10.1.1 Screening Assessments (Day -28 to Day 1)**

Trial specific assessments will only be conducted after patients have given written IC. This includes:

- a) Medical history
- b) Concomitant medication
- c) ECOG performance score
- d) Full blood count
- e) Biochemical series
- f) Assessment of menopausal status if it is not clinically evident (confirmed with LH, FSH and Oestradiol)
- g) AEs/SAEs (from time of consent)

Results from blood tests within 6-8 weeks prior to informed consent can be used in place of repeated blood results, unless repeat bloods tests are felt to be clinically indicated at the investigator's discretion.

[figure not shown]

### 10.1.2 Subject Registration/Randomisation

Registration and randomisation must be complete prior to the start of trial treatment. Patients will be registered following confirmation of eligibility (including results of screening assessments). Local site staff will complete the 'patient details', 'informed consent' (CRF not original consent form) and 'eligibility' CRFs and forward them to the central coordinating office to register the patient and provide authorisation to randomise. Appropriate staff at the local site will then randomise the patient upon confirmation of central approval. Data will be entered into a web-based central randomisation system (Sealed Envelope) by the relevant local site staff. The web-based central randomisation system will allocate patient trial numbers sequentially in the order in which the patients are randomised.

Supporting documentation required for patient randomisation will include results of an initial diagnostic core biopsy, specifically delineating ER status, histological subtype (ductal or lobular) and tumour grade, in addition to the patient details, IC and eligibility forms. These must be medically reviewed to confirm randomisation. Any queries must be resolved prior to randomisation. The PI or co-investigator will sign the eligibility CRF to confirm eligibility.

